## Abstract

**Abstract:**

**Introduction:**

Exposure to adverse childhood experiences (ACEs) is associated with a range of poor long-term health outcomes, including multimorbidity and chronic pain. Epidemiological evidence underpins much of this relationship; however, psychophysical testing methods, such as quantitative sensory testing (QST), may provide valuable insights into potential mechanisms. Previous studies have shown inconsistent links between ACEs and QST, but the QST profiles of people with multimorbidity have not been reported. We hypothesise that exposure to ACEs is associated with lowered QST thresholds (ie, experience of pain with milder stimuli) and that this association is stronger in adults with multimorbidity and/or chronic pain. The ACE-MAP study is a cross-sectional feasibility study with the primary aim of assessing the feasibility and acceptability of the proposed study procedures. The secondary aim is to generate preliminary data to understand the impact of ACEs on QST thresholds.

**Methods and analysis:**

We plan to recruit 40 participants, with 10 in each of the following groups: (1) chronic pain with multimorbidity; (2) chronic pain without multimorbidity; (3) multimorbidity without chronic pain; and (4) controls. Participants will complete a series of questionnaires (including on ACEs, chronic pain and long-term conditions) and will then take part in QST assessments. The primary study outcomes will include measures of feasibility and acceptability of the proposed study design. The secondary study outcomes will include exploratory analysis on the relationship between ACEs and QST thresholds.

**Ethics and dissemination:**

The study was approved by the Scotland B Research Ethics Committee (reference: 24/SS/0031). Results from the study will be presented at scientific conferences, published in a peer-reviewed journal and shared with patients and members of the public through other media streams.

**Trial registration number:**

ISRCTN10049430.

STRENGTHS AND LIMITATIONS OF THIS STUDYThis study was designed with active input from our patient and public involvement group, which consists of eight individuals with lived experience of adverse childhood experiences (ACEs), multimorbidity and chronic pain.The questionnaire on ACEs that will be used has been co-developed by members of the Consortium Against Pain Inequality and our patient and public involvement group. It covers a broad range of ACEs and is designed to be more acceptable to participants than existing questionnaires.This study will use both subjective and objective assessments of pain.This study is limited to participants who can speak English, so that their psychological and physical safety can be ensured by the study team during the completion of questionnaires and sensory testing.This is an exploratory study and therefore it will have a small sample size.

## Introduction

 Adverse childhood experiences (ACEs) are potentially stressful events or environments that occur before the age of 18. They may be subdivided into forms of abuse (eg, physical), neglect (eg, emotional), household challenges (eg, parental separation) and external challenges (eg, bullying). These experiences are remarkably common: a recent meta-analysis suggested that 61% of adults have experienced at least one type of ACE, while 16% have experienced four or more.^1^ In recent years, ACEs have been the focus of many epidemiological studies that have linked them to poor outcomes in a range of physical health, mental health and social parameters in adulthood.^2^,^10^ These studies have demonstrated a dose-dependent relationship: as the burden of ACE exposure increased, so too did the burden of adverse outcomes.

Some of this evidence base has linked ACE exposure with both chronic pain^10^,^13^ and multimorbidity.^2 9^ Chronic pain, defined as pain that persists or recurs for longer than 3 months, is a common problem affecting around 34% to 44% of people in the UK, with 12% of people having ‘high impact’ chronic pain that affects their ability to cope with daily activities.^14 15^ Multimorbidity, defined as the co-occurrence of two or more long-term conditions (LTCs) in the same individual, is also a common problem with a lifetime prevalence of 33%.^16^ Chronic pain and multimorbidity are closely related: many of the risk factors for chronic pain (eg, older age, female gender, deprivation) are also risk factors for multimorbidity.^17^,^19^ Furthermore, one study reported that 69% of participants with chronic pain reported another LTC (and therefore met the definition of multimorbidity), and participants with more than four LTCs were 3.6 times more likely to have chronic pain than those with no LTCs.^20^ Thus, chronic pain is often an important component of the burden of illness in people living with multimorbidity.

There are a number of potential explanations for the relationship between ACEs, chronic pain and multimorbidity. From epidemiological studies, we know that these include social vulnerability^21^ and shared genetic vulnerability.^22^ However, other study designs can provide further insights into underlying mechanisms and may help identify potential targets for intervention. Psychophysical measurements may provide additional insights: while pain is a subjective experience, it is possible to derive objective pain measurements by using validated structured techniques.

Quantitative sensory testing (QST) is a structured method of assessing sensory pathways, deriving numerical measurements from subjective sensations. QST tests can be either static or dynamic; static QST evaluates the basal state of the nociceptive system through measurement of sensory/pain thresholds, while dynamic QST evaluates mechanisms of pain processing by using more complex stimulation of the somatosensory system.^23 24^ Studies utilising static QST assessments have reported lower pain thresholds in people with a history of physical or sexual abuse^25 26^ and in those with a history of psychological trauma.^27 28^ Some studies utilising dynamic QST assessments have reported altered pain processing in people with a history of childhood trauma^29^ or ACEs,^30^ though others have reported no relationship.^31 32^ One of the challenges is that the methods of ACE assessment and the QST protocols used vary between studies.

QST is well-established in pain research in both adult and paediatric populations, but to our knowledge, the QST profiles of individuals with multimorbidity have not been investigated. Understanding how these sensory parameters may vary based on ACE exposure may provide insights into the mechanisms that underpin the associations between ACEs, multimorbidity and chronic pain that are repeatedly seen in epidemiological studies. Our hypothesis is that exposure to ACEs is associated with lowered QST thresholds (ie, experience of pain with milder stimuli) and that this association is stronger in adults with multimorbidity and/or chronic pain. This is based on the higher prevalence of chronic pain found in people who have experienced ACEs and subsequent LTCs.^20 33 34^

The ACE-MAP study is an observational feasibility study with the primary aim of assessing the feasibility and acceptability of the proposed study procedures in adult participants, including those living with multimorbidity and/or chronic pain. The secondary aim is to generate preliminary data to understand the impact of ACEs on QST thresholds.

The ACE-MAP study is part of a larger multi-institution collaboration, the Consortium Against Pain Inequality (CAPE), that is more widely looking at the relationship between ACEs and chronic pain.^35^

## Methods and analysis

### Patient and public involvement

This study has had input from members of our patient and public involvement group (the Chronic Pain Advisory Group – CPAG), who are part of CAPE.^35^ CPAG consists of eight individuals with lived experiences of ACEs, multimorbidity and chronic pain. Thus far, the group has provided feedback on the research question, the study design (including reviewing the potential participant burden), the participant-facing study materials and the provision of appropriate support for participants. Their involvement is ongoing.

### Design and setting

This is a single-site feasibility study with a cross-sectional design. Participants will be asked to attend one assessment session at Ninewells Hospital and Medical School, University of Dundee, UK.

### Recruitment

Potential participants will be identified through multiple streams:

The Scottish Health Research Register and Biobank (SHARE) database^36^ will be used to identify and invite potential participants that fulfil the inclusion criteria (based on SHARE data). Initial contact will be made by SHARE on behalf of the research team using established SHARE protocols. Potentially interested participants, who verbally consent to hearing more about the study, will be contacted by the research team.Patients who are referred to chronic pain clinics in NHS Tayside are invited to consent to receive information about future research studies. From those who have opted in, potential participants that fulfil the inclusion criteria will be contacted by a member of the clinical team. Potentially interested participants, who verbally consent to hearing more about the study, will be contacted by the research team.We designed advertising materials (study posters, website content) with input from our patient and public involvement group. Potential participants who see these materials or who learn of the study through word of mouth can contact the research team directly.

Potential participants identified through these streams will be contacted by the research team by phone and/or email and assessed for eligibility for participation. Inclusion/exclusion criteria for participation are:

Inclusion criteria:Age ≥18 years.Exclusion criteria:Lacks the capacity to consent to participate in the study.Unable to read or speak English to a sufficient standard to complete questionnaires or to follow instructions for sensory tests.

We will recruit participants to four groups: (1) chronic pain with multimorbidity; (2) chronic pain without multimorbidity; (3) multimorbidity without chronic pain and (4) a control group (people with neither multimorbidity nor chronic pain). We will use the list of LTCs reported by Ho *et al*^37^ in a Delphi consensus study^37^ to determine multimorbidity status (table 1). The inclusion and exclusion criteria for each group are listed in table 2. During the recruitment period, if it becomes evident that there is over-representation or under-representation from any of these groups the research team will prioritise the recruitment of individuals from specific groups to ensure an appropriate mix.

**Table 1 T1:** Long-term conditions included in the measure of multimorbidity

Body system (based on ICD-10 chapters)	Long-term condition
Cardiovascular disease	Stroke
	Coronary artery disease
	Heart failure
	Peripheral artery disease
	Heart valve disorders
	Arrhythmia
	Venous thromboembolic disease
	Aneurysm
	Hypertension (treated and untreated)
Metabolic and endocrine diseases	Diabetes
	Addison’s disease
	Cystic fibrosis
	Thyroid disorders
Respiratory disease	Chronic obstructive pulmonary disease
	Asthma
	Bronchiectasis
Neurological disease	Parkinson’s disease
	Epilepsy
	Multiple sclerosis
	Paralysis
	Transient ischaemic attack
	Peripheral neuropathy
Cancer	Solid organ cancers
	Haematological cancers
	Metastatic cancers
	Melanoma
	Benign cerebral tumours that cause disability
Mental and behavioural disorder	Dementia
	Schizophrenia
	Depression
	Anxiety
	Bipolar disorder
	Drug or alcohol misuse
	Eating disorder
	Autism
	Post-traumatic stress disorder
Musculoskeletal disease	Connective tissue disease
	Osteoarthritis
	Long-term musculoskeletal problems due to injury
	Osteoporosis
	Gout
Digestive disease	Chronic liver disease
	Inflammatory bowel disease
	Chronic pancreatic disease
	Peptic ulcer
Urogenital disorder	Chronic kidney disease
	End-stage kidney disease
	Endometriosis
	Chronic urinary tract infection
Haematological disorder	Anaemia (including pernicious anaemia and sickle cell anaemia)
Eye disease	Vision impairment that cannot be corrected
Ear disease	Hearing impairment that cannot be corrected
	Meniere’s disease
Infectious disease	HIV infection and AIDS
	Chronic Lyme disease
	Tuberculosis
	Post-acute COVID-19
Congenital disease	Congenital disease or chromosomal abnormalities

Adapted from Ho *et al*.^37^Ho et al. (2022).

ICD-10International Classification of Diseases (10th Revision)

**Table 2 T2:** Inclusion and exclusion criteria

Chronic pain with multimorbidity group	Chronic pain without multimorbidity group	Multimorbidity without chronic pain group	Control group
Inclusion criteria: Age ≥18 years Has ≥1 of the LTCs listed in table 1 Has a diagnosis of chronic pain AND/OR has had persistent or recurring pain lasting >3 months	Inclusion criteria: Age ≥18 years Has a diagnosis of chronic pain AND/OR has had persistent or recurring pain lasting >3 months	Inclusion criteria: Age ≥18 years Has ≥2 of the LTCs listed in table 1	Inclusion criteria: Age ≥18 years
Exclusion criteria: Lacks the capacity to consent to participate in the study Unable to read or speak English to a sufficient standard to complete questionnaires or to follow instructions for sensory tests	Exclusion criteria: Lacks the capacity to consent to participate in the study Unable to read or speak English to a sufficient standard to complete questionnaires or to follow instructions for sensory tests. Has ≥1 of the LTCs listed in table 1	Exclusion criteria: Lacks capacity to consent to participate in the study Unable to read or speak English to a sufficient standard to complete questionnaires or to follow instructions for sensory tests. Has a diagnosis of chronic pain, AND/OR has had persistent or recurring pain lasting >3 months	Exclusion criteria: Lacks the capacity to consent to participate in the study Unable to read or speak English to a sufficient standard to complete questionnaires or to follow instructions for sensory tests. Has ≥2 of the LTCs listed in table 1 Has a diagnosis of chronic pain, AND/OR has had persistent or recurring pain lasting >3 months

LTC, long term condition

Recruitment will open in July 2024 and is predicted to close by the end of 2025.

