Thermal detection and pain thresholds will be measured at the forearm or hand using a Modular Sensory Analyser with a standard 25×50 mm thermode (Somedic SenseLab, Sweden). Starting from a baseline temperature of 32°C, we will use the ramp method with a rate of change of 1°C/s. The lower and upper cutoffs will be 10°C and 50°C, respectively. Participants will be instructed to press a button at the appropriate point for each test; for the cold detection threshold and warm detection threshold, this will be when they ‘first feel a [cold/warm] sensation’ at the test site; and for the cold pain threshold and the heat pain threshold, this will be when they ‘first feel something that is painfully [cold/warm]’ at the test site. For each parameter, we will take three measurements and calculate the mean. The result of the TSL test, in which alternating cold and warm stimuli are applied, will be the number of paradoxical heat sensations reported (ie, where cold is reported as warm and vice versa).The mechanical detection threshold will be measured at the forearm or hand using a standardised calibrated set of von Frey filaments (Somedic SenseLab, Sweden) that exert forces of 0.63 mN to 235.36 mN on bending. With their eyes closed, participants will be asked to verbally report when they feel something touch the test site. Using the method of limits, we will take five detection threshold measurements and report the geometric mean.The mechanical pain threshold will be measured at the forearm or hand using calibrated weighted PinPrick stimulators (MRC Systems, Germany) that exert forces from 8 mN to 512 mN. With their eyes closed, participants will be asked to verbally report when they feel something sharp at the test site. Using the method of limits, we will take five pain threshold measurements and report the geometric mean.Stimulus response functions will be measured at the forearm or hand using the same PinPrick stimulators as described above and three light tactile stimulators: cotton wisp exerting a force of ~3 mN, a cotton wool tip attached to an elastic strip exerting a force of ~100 mN and a standardised brush (Somedic SenseLab, Sweden) exerting a force of ~300 mN. Stimuli will be applied in a pseudorandom sequence (consistent across all participants) with approximately a 10 s interval between stimuli. With their eyes closed, participants will be asked to verbally report a pain score for each stimulus on a numerical rating scale of 0 to 100. Mechanical pain sensitivity will be calculated as the geometric mean of the pain scores for all pinprick stimuli. Dynamic mechanical allodynia will be calculated as the geometric mean of the pain scores for all light tactile stimulators.Wind-up ratio (WUR) will be measured at the forearm or hand using the 256mN PinPrick stimulator. A single stimulus will be applied followed by a series of 10 stimuli to the same area. With their eyes closed, participants will be asked to verbally report two pain scores on a numerical rating scale of 0 to 100, one for the single stimulus and one for the series of 10. We will repeat this five times. The WUR will be calculated as the mean pain score for the series divided by the mean pain score for the single stimulus.The vibration detection threshold (VDT) will be measured at a bony prominence at the wrist or elbow using a 64 Hz Rydel-Seiffer graded tuning fork (Ragg Tuning Forks, UK). With their eyes closed, participants will be asked to verbally report when they feel the vibration sensation stop at the test site. We will take three measurements and calculate the mean.The pressure pain threshold (PPT) will be measured at the thenar eminence with an algometer (Somedic SenseLab, Sweden). Participants will be asked to verbally report when they ‘first feel pain’ at the test site. We will take three measurements and calculate the mean.CPM will be measured using the cold pressor test. The participant will be asked to lower their non-dominant hand into a cold water bath at 10°C±2°C (the conditioning stimulus). The water temperature will be generated by a Grant LTC4 refrigerated circulating bath (Grant Instruments, UK). After 20 s, we will measure two modalities of test stimuli on the dominant arm; PPT followed by HPT, as described above. We will take three measurements of each and calculate the mean. CPM will be reported as an absolute value (the mean PPT or HPT prior to the conditioning stimulus minus the mean PPT or HPT during the conditioning stimulus) and as a percentage change (absolute CPM divided by the mean PPT or HPT prior to the conditioning stimulus). Thus, a negative CPM value will indicate CPM-induced pain inhibition.^42^ We will also measure the duration of time that the hand was submerged in the cold water bath (up to a maximum of 120 s) and ask the participant to verbally report a pain score for the water bath on a numerical rating scale of 0 to 100.

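### Conditions that can alter sensation at the test site count towards multimorbidity in three of the four groups, and nothing described records whether the tested limb is affected

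*Protocol article*

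**What the plan says.** - **Grouping.** The Recruitment section uses a consensus list of long-term conditions (LTCs) "to determine multimorbidity status (table 1"). The list includes stroke under cardiovascular disease, and paralysis, "Multiple sclerosis" and "Peripheral neuropathy" under neurological disease.
- **Eligibility.** The article states that "The inclusion and exclusion criteria for each group are listed in table 2". Two exclusions apply to every group: lack of capacity, and "Unable to read or speak English to a sufficient standard to complete questionnaires or to follow instructions for sensory tests". Neither concerns sensation.
- **Group differences.** Chronic pain with multimorbidity requires "Has ≥1 of the LTCs listed in table 1 Has a diagnosis of chronic pain" or persistent pain, so one listed condition is enough. Multimorbidity without chronic pain requires two or more. Chronic pain without multimorbidity excludes anyone who "Has ≥1 of the LTCs listed in table 1". Controls are excluded only from two listed conditions upwards, so they may have one.
- **Measurement.** In Procedure, "The mechanical pain threshold will be measured at the forearm or hand using calibrated weighted PinPrick stimulators". Thermal and touch thresholds use the same region, vibration uses the wrist or elbow, and pressure uses the thenar eminence. All tests are bilateral except CPM, which conditions the non-dominant hand and tests the dominant arm.
- **Timing.** LTCs, pain and medication are collected by questionnaire before QST. There is one session and no planned follow-up.
- **Use.** Statistical analysis describes exploratory work on ACE count against QST parameters, and on how that varies with multimorbidity and chronic pain status. The results feed the design and sample size of the definitive study.

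**The concern.** A condition that can change sensation in the hand helps to decide which group a person is in, and sensation in that hand is then the outcome. Three groups are open to this and one is not. A difference between groups, or in the ACE-QST relationship across groups, could therefore partly reflect lesions of the sensory pathway instead of altered pain processing. With 10 people per group, a single extreme value carries weight in both the mean and the SD.

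The secondary QST findings and the planning inputs for the next study are at stake. The missing information is also hard to recover later. The LTC questionnaire, as described, shows who has a diagnosis, but not whether it affects the tested limb or which side. No later analysis plan can reconstruct that.

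**Working it through.** **The plan's own figure.** 4 groups × 10 = 40, as stated. No SD, effect size, power or expected prevalence is given, so there is no power figure to reproduce. Everything below is illustrative.

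**Step 1. Who can have one of the four conditions, from Tables 1 and 2**

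| Group | Listed conditions allowed | Can include stroke, MS, paralysis or neuropathy? |
|---|---|---|
| Chronic pain with multimorbidity | 1 or more | Yes; one alone qualifies |
| Chronic pain without multimorbidity | 0 | No |
| Multimorbidity without chronic pain | 2 or more | Yes |
| Control | 0 or 1 | Yes, one |

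**Step 2. Chance that a group of 10 contains at least one.** The formula is 1 − (1 − p)^10, with p assumed. For p = 5%, 10%, 20% and 30% it gives 40%, 65%, 89% and 97%. Here p should be read as the share whose tested limb is affected, which is no larger than the share with a diagnosis.

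**Step 3. Shift in a group's average.** Device limits come from Procedure. The level of the other participants is assumed, and a person who never responds is assumed to be scored at the limit.

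- Pinprick, limit 512 mN, averaging across participants on the log scale (assumed): factor = (512 / typical)^(k/10), where k is the number affected.
  - k = 1: (512/128)^0.1 = 1.15; (512/64)^0.1 = 1.23; (512/32)^0.1 = 1.32.
  - k = 2: 1.32, 1.52 and 1.74 for the same typical values.
- Touch, limit 235.36 mN, k = 1: (235.36/4)^0.1 = 1.50; (235.36/2)^0.1 = 1.61; (235.36/1)^0.1 = 1.73.
- Heat pain, limit 50°C, k = 1: (50 − 46)/10 = 0.4°C to (50 − 42)/10 = 0.8°C.

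For scale, the pinprick set spans 8 to 512 mN, which is six doublings. A factor of 1.15 to 1.32 is 0.2 to 0.4 of one doubling.

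**Step 4. Effect on the planning SD.** If a fraction f of a group is displaced by d SD, its variance is multiplied by 1 + f(1 − f)d².

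- f = 0.1, d = 2: 1 + 0.09 × 4 = 1.36, so the SD is multiplied by 1.17.
- f = 0.1, d = 4: 1 + 0.09 × 16 = 2.44, so the SD is multiplied by 1.56.

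Required n scales with the variance, so planning from that one group's SD would multiply n by 1.36 to 2.44. If the SD is pooled over four equal groups and only one is affected, the variance factor falls to (3 + 1.36)/4 = 1.09 up to (3 + 2.44)/4 = 1.36.

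**The case against.** Several objections carry weight.

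- **Estimand.** The study sets out to describe QST in people with multimorbidity, and these conditions belong to multimorbidity under the list it adopted. The Introduction also speaks of LTCs that follow ACEs, so they may lie on the pathway of interest. Dropping affected people from the main analysis would change the question. This stands, and the main analysis should stay as it is.
- **The analysis plan.** Choice of side and sensitivity analyses are commonly left to an analysis plan, which is not shown. This stands for the analysis rule. It does not answer the data-collection gap in a single-visit study, although a case report form that is not shown may already contain such an item.
- **Planning SD.** If the definitive study keeps the same eligibility and analyses everyone, the SD that includes affected people is the right one. This stands, and it is a reason to report both.

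A reader might infer more than the document supports:

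- *That the comparisons are biased by design, in a known direction.* Lesions can raise thresholds or cause hypersensitivity. The article names no specific contrast with the chronic-pain-only group. The ACE-QST slope is biased only if being affected is related to ACE count; otherwise affected people add noise.
- *That one or two people would hide or reverse a group difference.* No SD or expected difference is given, so this cannot be shown.
- *That a listed diagnosis means an insensate hand.* It does not; the calculations with device limits are extreme cases.
- *That the chronic-pain-only group is free of nerve injury.* It is free only of listed conditions.

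**Conclusion.** The point holds as a modest one. Three of the four groups can include people with listed conditions that may alter sensation at the test site, and the article describes no record of whether the tested limb is affected. The possible result is added noise, or distortion that differs between groups, in the secondary exploratory QST results and in the planning SD.

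The direction is not fixed and the size is unknown. The factor of 1.15 to 1.32 for pinprick rests on three assumptions: one fully insensate participant in 10, scoring at the device limit, and the other nine at 128 to 32 mN. The SD factor of 1.17 to 1.56 within one group rests on an assumed displacement of 2 to 4 SD. The primary feasibility and acceptability outcomes are not touched.

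**What to change.** Leave eligibility and the all-participant analysis unchanged, and add two things.

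1. **At the session,** record for each side whether any neurological condition or nerve injury, listed in Table 1 or not, affects sensation at the tested forearm or hand, including the wrist or elbow site used for vibration. Ask this in all four groups.
2. **In the analysis,** add a sensitivity analysis of the ACE-QST results, the group results and the planning SD. It uses only unaffected sides and omits participants affected on both sides. Since CPM involves both limbs and has no alternative side, omit a participant's CPM result from this analysis if either limb is affected.

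Report the two sets of results side by side, so that the definitive study can take the SD that matches its own population. The cost is one extra form item per side and a few fewer QST values in the sensitivity analysis. The multimorbidity groups are likely to lose most of these, so the number omitted per group should be shown.
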